**Fig 8 pone.0331177.g008:**
[figure not shown]
The experimental protocol will begin with a preliminary motor imagery run without NF for calibration, consisting of five alternating 15-second rest and task periods (MI task of the left upper limb). This will be followed by three conditions: two EEG-fNIRS runs, two EEG-based NF runs and two fNIRS-based runs, in randomized order across the participants. Each run will follow a block design, consisting of ten alternating 15-second rest and task periods. The NF score will be calculated based on the brain activity over the right primary motor cortex), corresponding to C4-EEG electrode and D1-S1/D2-S2 FNIRS channels in our layout.

**Neurofeedback evaluation.** In accordance with the CRED-nf checklist [66], the subjective feeling of success and the mental strategies used to control the ball movement will be gathered during an interview after the two runs of each NF condition. Participants will have to fill out a custom-made form asking: i) the type of movement imagined during the runs; ii) the strategy used for the task (open question); iii) the level of the MI kinesthetic and visual information; iv) the level of sleepiness; v) the feeling of controlling the NF; and vi) the feeling of ability to disengage from the MI task at rest.

#### 2.2.4. *Data and outcome measures.*

All outcome measures are presented in Table 1, organized according to the timing of the experiment (before the experiment, calibration session, EEG-based NF condition, fNIRS-based NF condition and EEG-fNIRS-based NF condition). Additionally, we will collect participants’ age, gender as well as their previous experience with NF and MI, their use of the left upper limb in specific physical or artistic activities (e.g., music, sports), the quality and quantity of sleep before the experiment and their awareness level.

**Table 1 pone.0331177.t001:** Study outcomes assessments before the NF experiment (column “Pre-NF”), during the calibration of the MI task (column “Calib”) and for each experimental condition (columns “EEG-NF”, “fNIRS-NF” and “EEG-fNIRS-NF”).

Outcomes measures	Pre-NF	Calib	EEG-NF	fNIRS-NF	EEG-fNIRS-NF
Quantity and quality of sleep	X				
MI vividness (KVIQ)	X		X	X	X
Awarness level (Stanford scale)	X		X	X	X
VAS – feeling of controlling the gauge			X	X	X
VAS – feeling of disengagement at rest			X	X	X
Strategies used to do the NF task			X	X	X
Brain activity (EEG/fNIRS)		X	X	X	X
NF scores			X	X	X

**Motor imagery abilities.** We will assess participants’ general MI ability before starting the experiment using the short version of the Kinesthetic and Visual Imagery Questionnaire (KVIQ-10, Malouin et al., 2007 [67]). The KVIQ evaluates the vividness of MI for five simple movements. For each movement and MI modality (visual and kinesthetic), participants will be asked to: i) physically perform the movement, ii) imagine the movement and then self-rate the vividness of their MI on an analog scale from 1 (no image or kinesthetic sensation) to 5 (image as clear as during the actual movement, with similar perceived sensations). Participants will also self-report their MI vividness after each NF condition using the same visual and kinesthetic scales as those in the KVIQ-10.

**Sleepiness level.** Before starting the experiment and after each condition, participants will rate their sleepiness level using the Stanford Sleepiness Scale [68], with a range from 1 (fully awake) to 8 (sleeping). Prior to the experiment, participants will also report the sleep quality from the previous night on a Likert scale from 1 (very poor) to 5 (very good) and the number of hours they slept.

**Mental strategies for neurofeedback.** After each of the three NF conditions, participants will complete a questionnaire about the strategies they used during the task. Questions will be: “What type of movement did you imagine to move the ball?” and “Describe the strategy you used to perform the task” (e.g., ball fixation, focus, self-encouragement, visualization, etc.). Additionally, participants will rate their feelings of control over the gauge and their ability to disengage from the MI-NF task using a visual analogue scale (VAS). They will be asked: “Did you feel like you were in control of the gauge?” and “Did you feel it was easy to disengage from the task?” The VAS consists of a straight line, where 0 represents “not at all” and 10 represents “totally”.

**Neurofeedback scores.** All fNIRS-based and EEG-based NF scores (*NF*_*fNIRS*_, *NF*_*EEG*_ and *NF*_*fNIRS-EEG*_) will be stored and organized according to the condition (EEG, fNIRS, EEG-fNIRS) and the run [1,2]. Within each run, all scores will be averaged to produce a global NF score per condition and per run. Moreover, the time course of the scores will be extracted. The process for calculating these scores is outlined in the section Neurofeedback score.

**Brain activity.** Sensorimotor cortical region activation will be measured during the seven steps of the experiment (MI pre and two runs for each of the three conditions). For offline analysis, the fNIRS signal will be preprocessed in the same manner as during real-time processing (see Section fNIRS online processing), with the exception of a more detailed inspection of the channel quality, and the use of the whole signal for optical density conversion, short-channel correction and HB states. For the quality check, we will assess the scalp-coupling index and peak spectral power for each channel, condition and run [69–71]. Channels that meet the quality check criteria will be included in the offline analysis. We will examine changes in the average, peak and area under the curve of ΔHbO_2_ and ΔHbR concentration in the contralateral (right) and ipsilateral (left) sensorimotor cortical regions during the three conditions (EEG-NF, fNIRS-NF, EEG-fNIRS-NF). For offline analysis, the EEG signal will be preprocessed in the same manner as during real-time processing (see Section EEG online processing), but adding an independent component analysis to better remove extra-cortical activity such as eye blinks, Hyvarinen, 1999 [72]). The changes in sensorimotor cortex neural oscillations will be assessed by examining the magnitude and ratio of alpha- and beta-frequency power in both the ipsilateral and contralateral motor cortical regions during rest and the NF task. The event-related desynchronization (ERD, power decrease during the task) and event-related synchronization (ERS, power increase during rest) of the alpha motor mu rhythm (8–13 Hz) and beta rhythm (13–35 Hz) will be calculated for each run and averaged according to the condition (EEG, fNIRS, EEG-fNIRS) and run [1,2].

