**Methods:**

We developed a custom experimental platform, including a cap integrating EEG and fNIRS sensors, along with software for real-time signal processing, NF score calculation and visual feedback presentation. To evaluate the effect of EEG-fNIRS NF in the context of MI, thirty right-handed participants will undergo three randomized NF conditions: EEG-only, fNIRS-only and EEG-fNIRS based NF. EEG electrodes and fNIRS channels will be positioned above the sensorimotor cortices. Participants will be presented with a visual representation of a ball along a one-dimensional gauge moving upwards according to their brain activity level as they perform a MI task of their left-hand. An NF score will be computed from the right primary motor cortex activity along the three different experimental conditions (EEG-only, fNIRS-only, EEG-fNIRS). The association between the NF score, the neuroimaging modality and the motor imagery strategy will then be analyzed.

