**Fig 2 pone.0331177.g002:**
[figure not shown]
Epoching of the EEG and fNIRS signals. 1-A represents the epochs averaged for the rest period and 1-B for the task for the EEG signal. 2-A represents the epochs averaged for the rest period and 2-B for the NF task for the fNIRS signal.

$Ratio\;ERD=\frac{\left(pTask\;-pRest\right)}{pRest}*100$, where *pRest* represents the power averaged from the epochs from the last 5 s of the preceding rest period and *pTask* represents the power averaged from the last 1.5 s that capture the near-instantaneous power during the NF task [53]. A new ERD ratio is calculated every time a new epoch is received (i.e., every 0.25 s according to the time based epoching). During the calibration session, the 30th percentile of the ERD ratios is extracted from all the calibration blocks and set as the target level to reach 100% during the NF session. This choice was made based on previous NF protocols, in order to individually set the difficulty of the NF task (i.e., maximal value of the gauge). We chose to focus solely on the expected movement-related desynchronization, which is indicated by a negative ERD during the task [54]. This value is stored and used to compute the EEG-NF score: $NF_{EEG}=\;\frac{Ratio\;ERD\;(NF\;task)}{Ratio\;ERD\;(calibration)}*100$.

**fNIRS**-**NF score.** A time-based epoching is applied to generate epochs of 0.96 s every 0.48 s for the fNIRS (see Fig 3). The duration of the epochs and moving window of the fNIRS is based on the sampling frequency (i.e., 6.25 Hz), ensuring a constant and integer number of fNIRS samples across all epochs. A fNIRS NF score is calculated every 0.48 s based on 1.92 s periods (i.e., averaged of 3 epochs) using a 4.8 s rest periods (i.e., average of 9 epochs, see Fig 2). In order to prevent from temporal drift, the fNIRS-NF score is computed considering the last 4.8* seconds of the previous rest period as the baseline. The **diff*Δ*HbO**_*2*_ is then calculated as followed:

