**Fig 3 pone.0331177.g003:**
[figure not shown]
Implementation of EEG and fNIRS from acquisition and real-time preprocessing of EEG and fNIRS signals to the calculation of the NF score. 1. Acquisition is done through the OpenViBE acquisition server for the EEG, and for the fNIRS the raw signal is recorded via the NIRStar software and transferred to the openViBE acquisition software via LSL communication. 2. Real-time preprocessing steps are conducted in the OpenViBE designer software.

**diff*Δ*HBO**_*2*_* = ΔHBO*_*2(Task)*_
**-* Δ*HBO**_*2(Rest*)_*,* where *ΔHBO*_*2(Rest)*_ represents the average of the epochs from the last 4.8 s of the preceding rest period and *ΔHbO*_*2(Task)*_ represents the average over the last 1.92 s reflecting the near-instantaneous relative variation in oxyhemoglobin concentration during the NF [49]. A new ΔHbO_2_ value will be calculated every 0.48 s. To follow the EEG targets, during the calibration session, the 30th percentile of the positive ΔHbO_2_ values as the target level to reach 100% during the NF session. This value will be stored and used to compute the fNIRS NF score:

$$\;NF_{fNIRS}\;=\;\frac{diff\Delta HBO_{2}\;(NF\;task)}{diff\Delta HBO_{2}\;(calibration)}*100.$$

We focus specifically on the expected response during movement, an increase in the relative ΔHBO_2_ concentration during the task is expected, which is reflected by a positive ΔHbO_2_ [55].

**EEG-fNIRS-NF score.** The EEG-fNIRS combined score is based on the average of the *NF*_*EEG*_ and *NF*_*fNIRS*_ scores. It is refreshed every time a new EEG or fNIRS score is calculated:

$$NF_{EEG\text{-}fNIRS}\;=\;\frac{{NF}_{EEG}+{NF}_{fNIRS}}{2}.$$

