**Neurofeedback score metaphor.** The implementation of the score metaphor is presented on Fig 4. We chose a visual feedback adapted from the work of Perronnet et al. (2020) [28]. The NF paradigm includes the use of a visual metaphor consisting of a vertical gauge with a yellow ball moving up and down in 1D. The ball position represents the EEG scores, fNIRS scores or the average of both EEG and fNIRS scores. The background of the 1D gauge is divided into four regions to provide the subject with reference points. The NF score calculation is carried out using a dedicated Python code (Python 3.12). Visual instructions and feedback are presented to the user using the PsychoPy toolbox (Peirce et al., 2019, version 2023.2.3 [60]). The ball position ranges from 0% to 100%. If the NF score exceeds 100%, it is capped at 100%, and if it is negative, it is set to 0%. Both the *NF*_*EEG*_ and *NF*_*fNIRS*_ score is transmitted to the Python Psychopy script through LSL and the ball position is updated accordingly. Every time a new score arrives, the ball position is updated.

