#### 2.2.1. *Participants.*

Thirty healthy adults will be recruited. The inclusion criteria are i) 18-year-old or older, and ii) right-handed (score > 0.5 Edinburgh inventory, Oldfield, 1971 [61]). The non-inclusion criteria are i) to report a neurologic or psychiatric disease, ii) to report left upper limb (UL) orthopedic issues. All participants will have to read an information letter and sign an informed consent form before participating in the experiment.

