#### 2.2.5. *Statistical analysis.*

Statistical analysis will be performed using the latest version of the R software. A significance level of p < 0.05 will be used for all analyses. The primary outcome will be the difference in the brain activity between the three conditions: EEG-based NF, fNIRS-based NF and EEG-fNIRS-based NF. To check that the participant has succeeded, at least to some extent, in performing the neurofeedback task in each condition, we will study the NF scores. The exploratory outcomes will include the perception of control over the gauge and the strategies employed in relation to the NF condition as well as the link between the MI abilities and the performance at the NF-task. To assess the normality of the NF scores and brain activity data (i.e., EEG-ERD, EEG-ERS, fNIRS-HbR, fNIRS-HbO_2_), the Shapiro-Wilk test will be conducted. If the data are normally distributed, parametric repeated measures ANOVA will be used for mean comparisons. In cases where the data do not follow a normal distribution, non-parametric Friedman tests will be employed to evaluate differences among conditions. The perception of control over the gauge, as a function of the NF condition, will also be compared using the Friedman test. Lastly, as an exploratory analysis, Pearson correlation coefficient will be used to examine the relationship between the feeling of NF control, the MI abilities and the NF scores, depending on the NF condition.

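### The neurofeedback (NF) score is compared among conditions although, on the natural reading, each condition's score has its own scale, so a modality effect can appear with identical brain activity

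*Protocol article*

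**What the plan says.** Section 2.1.3 defines three scores.

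- The EEG score is the event-related desynchronization (ERD) ratio during the task divided by a calibration target: "the 30th percentile of the ERD ratios is extracted from all the calibration blocks and set as the target level to reach 100"%. A negative ERD is the wanted direction.
- The fNIRS score is the task-minus-rest change in oxyhaemoglobin divided by its own target: "the 30th percentile of the positive ΔHbO_2_ values as the target level to reach 100% during the NF session". A positive change is the wanted direction.
- The combined score is the arithmetic mean of these two.

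Section 2.1.4 shows the participant a different score in each condition: "The ball position represents the EEG scores, fNIRS scores or the average of both EEG and fNIRS scores". The display is limited to 0 to 100%.

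Section 2.2.4 stores all three score types by condition and run, and then: "Within each run, all scores will be averaged to produce a global NF score per condition and per run". It does not say which stored score is the global one, or whether it is capped.

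Section 2.2.5 opens the testing route with "To assess the normality of the NF scores and brain activity data". Repeated-measures ANOVA follows if the data are normal, and Friedman tests among conditions if not. The threshold is common to all: "A significance level of p < 0.05 will be used for all analyses". The same section makes brain activity the primary outcome and gives the NF scores the role of checking that participants had some success in each condition. The abstract adds: "The association between the NF score, the neuroimaging modality and the motor imagery strategy will then be analyzed".

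**The concern.** A test among conditions has a clear meaning only if the same quantity is measured in each. Here the EEG condition would contribute a percentage of an alpha-power target, the fNIRS condition a percentage of a haemoglobin target, and the combined condition an average of the two. The quantities differ in numerator, in how hard the target is, in noise and in how strongly the 0 to 100 limit bites. A difference in means would then reflect scaling as well as performance.

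At stake is the secondary NF-score comparison and the association of NF score with modality announced in the abstract. An artefact there could be read as support for the hypothesised multimodal advantage. Under identical activity the capped combined score exceeded the EEG score at every equal response size from 0.25 to 2.

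**Working it through.** **Inputs from the article.** Thirty participants, each in all three conditions ("Thirty healthy adults will be recruited"); alpha 0.05; the two calibration rules; the combined score as a mean; the 0 to 100 limit on the display. The article gives no power or error-rate figure to reproduce. Its epoch counts do reproduce: (5 − 1)/0.25 + 1 = 17 and (1.5 − 1)/0.25 + 1 = 3 for EEG; (4.8 − 0.96)/0.48 + 1 = 9 and (1.92 − 0.96)/0.48 + 1 = 3 for fNIRS.

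**Assumption.** Response sizes are not given. Let both signals be normal with unit SD and a mean response *d* in the wanted direction, with *d* from 0 to 2, and let activity in the NF runs equal activity at calibration.

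**Step 1: target difficulty.** For EEG the wanted direction is downwards, so 30% of epochs lie at or beyond the 30th percentile, whatever *d* is. For fNIRS, 70% of the positive values lie above the target, which is 0.7 × Φ(*d*) of all values:

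- *d* = 0: 0.7 × 0.5 = 35%
- *d* = 0.5: 0.7 × 0.6915 = 48%
- *d* = 1: 0.7 × 0.8413 = 59%
- *d* = 2: 0.7 × 0.9772 = 68%

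**Step 2: expected uncapped scores.** The EEG target is *d* + 0.524, so the expected score is 100*d*/(*d* + 0.524). The fNIRS target is *t* = *d* + Φ⁻¹(1 − 0.7Φ(*d*)), so the expected score is 100*d*/*t*. The combined expectation is the mean of the two and must lie between them.

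| *d* | EEG target | fNIRS target | EEG score | fNIRS score | Combined |
|---|---|---|---|---|---|
| 0 | 0.524 | 0.385 | 0 | 0 | 0 |
| 0.25 | 0.774 | 0.454 | 32 | 55 | 44 |
| 0.5 | 1.024 | 0.540 | 49 | 93 | 71 |
| 1 | 1.524 | 0.775 | 66 | 129 | 97 |
| 2 | 2.524 | 1.521 | 79 | 131 | 105 |

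Mean capped scores (EEG/fNIRS/combined, averaged and then capped) were 45/51/48, 50/59/57 (57.5 before rounding down), 59/72/73 and 72/87/87 for *d* = 0.25, 0.5, 1 and 2.

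**Step 3: false-positive rate.** Trials of 30 participants were simulated with autocorrelated epochs and the same activity distribution in all conditions, 100 replicates per setting. Each entry is the share with p < 0.05.

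| *d* | ANOVA capped / uncapped | Friedman capped / uncapped |
|---|---|---|
| 0.25 | 72% / 32% | 58% / 37% |
| 0.5 | 97% / 94% | 86% / 96% |
| 1 and 2 | 100% / 100% | 100% / 100% |

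A separate simulation of the same null gave about 4 to 11% at *d* = 0, 35 to 61% at 0.25, 91 to 97% at 0.5, and 100% at 1 or more.

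**Step 4: sensitivity.** EEG power was made log-normal with a drop of 10, 30 or 50%, and the fNIRS response was set separately at 0, 0.25, 0.5 or 1, capped and uncapped (24 settings). ANOVA rejected in 80% or more in 18 of the 24. The other six gave 9, 16, 16, 38, 52 and 57%. The three lowest arose where the mean scores happened to lie close together; for example, with a 30% drop, a response of 0.5 and capping, the means were 56, 59 and 57.

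**Step 5: like for like.** When the same score was compared across all three conditions under the same null, the rejection rate was 1 to 9% (ANOVA) and 3 to 8% (Friedman). With 100 replicates the standard error at 5% is √(0.05 × 0.95/100) = 2.2 points, so this is consistent with nominal. Changing only the fNIRS target to the 70th percentile of positive values did not cure the problem: ANOVA still rejected in 10 to 98%.

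**The case against.** The strongest reply is that the article never says outright that displayed scores are compared. Section 2.2.4 stores every score type by condition, and section 2.1.4 passes both unimodal scores to the feedback script, so a like-for-like comparison may be what is intended. Section 2.2.5 describes the NF scores as a success check in each condition, which is a within-condition question. The abstract speaks of an association and names no test of means. All this is fair, and the displayed-score comparison is the natural reading rather than a stated one. It does not remove the problem. The article fixes the score formulas, a single global score per condition and the test among conditions, and nowhere says that the same score is used throughout.

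A reader might infer that a false modality finding is close to certain. The documents do not support that: the rate depends on response sizes and capping, which they do not give, and it can be near 5%. A reader might also infer that the trial's main conclusion is compromised. It is not, because section 2.2.4 measures brain activity with the same quantities in every condition.

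It can also be objected that uncapped scores are ratios, and that a small fNIRS target would give extreme values. That stands, so the choice between capped and uncapped should be declared rather than dictated here.

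**Conclusion.** The point holds for the secondary NF-score comparison and for the association of NF score with modality. On the natural reading, the three global scores have different numerators and targets of different difficulty, so a significant condition effect cannot be taken as a difference in performance. The uncapped combined score is by construction an average of the other two. Under identical activity its expectation lies between theirs, so it cannot exceed the better single modality unless activity itself differs.

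Under the null with 30 participants the error is usually far above 5%: roughly 35 to 60% at a standardised response of 0.25 (32 to 72% across tests and capping in one set of runs), over 90% in most settings at 0.5, and near 100% at 1 or more. With equal responses and symmetric noise it is near nominal when there is no response, and in other settings when the two scales coincide. These figures rest on assumed response sizes and noise. The asymmetry of the targets and the averaging follow from the article's own formulas.

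**What to change.** State in sections 2.2.4 and 2.2.5 that the EEG score and the fNIRS score are each computed in all three conditions, against the participant's single calibration target for that signal. Both systems record throughout the session (section 2.2.2), so this is feasible. Compare the EEG score across conditions and the fNIRS score across conditions as two separate analyses. State in advance whether capped or uncapped values are analysed. Use the displayed score only descriptively, or as a within-condition check of success, and align the abstract's sentence on modality with this.

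The cost is a change of wording and no new data. The small downside is two tests instead of one, partly overlapping the planned ERD and oxyhaemoglobin comparisons.

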#### 2.2.5. *Statistical analysis.*

Statistical analysis will be performed using the latest version of the R software. A significance level of p < 0.05 will be used for all analyses. The primary outcome will be the difference in the brain activity between the three conditions: EEG-based NF, fNIRS-based NF and EEG-fNIRS-based NF. To check that the participant has succeeded, at least to some extent, in performing the neurofeedback task in each condition, we will study the NF scores. The exploratory outcomes will include the perception of control over the gauge and the strategies employed in relation to the NF condition as well as the link between the MI abilities and the performance at the NF-task. To assess the normality of the NF scores and brain activity data (i.e., EEG-ERD, EEG-ERS, fNIRS-HbR, fNIRS-HbO_2_), the Shapiro-Wilk test will be conducted. If the data are normally distributed, parametric repeated measures ANOVA will be used for mean comparisons. In cases where the data do not follow a normal distribution, non-parametric Friedman tests will be employed to evaluate differences among conditions. The perception of control over the gauge, as a function of the NF condition, will also be compared using the Friedman test. Lastly, as an exploratory analysis, Pearson correlation coefficient will be used to examine the relationship between the feeling of NF control, the MI abilities and the NF scores, depending on the NF condition.

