**Discussion:**

The designed experimental platform allows combined EEG-fNIRS NF. The presented study protocol will be the first investigation of the effects of multimodal neurofeedback using EEG and fNIRS during upper-limb MI tasks. We hypothesize that presenting the participants with a visual NF representing a score based on both EEG and fNIRS signals will result in more specific task-related brain activity in the sensorimotor cortices. With potentially increased neuroplasticity, such a system could find applications in clinical contexts, particularly in motor rehabilitation, for example in post-stroke units.

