Although multimodal EEG-fNIRS is considered to combine the advantages of EEG and fNIRS in a way that compensates for the limitations of each modality, its potential to record cerebral activity features has not been comprehensively investigated [26]. In motor rehabilitation, motor imagery (MI) – the mental representation of an action without its actual execution [42] – is commonly incorporated into NF protocols to target brain motor areas, making it a suitable task for anticipating later clinical application [9]. To our knowledge, no study has explored the effect of multimodal EEG-fNIRS-based NF in the context of MI. Thus, the aim of this paper is to evaluate the efficiency of EEG-fNIRS-based NF for MI in comparison to unimodal EEG-based and fNIRS-based NF. To reach this objective, we developed and implemented an experimental platform for multimodal EEG-fNIRS NF in the context of upper limb (UL) MI. Implementing such multimodal systems presents significant challenges, including the need for seamless coordination and synchronization of two inherently distinct systems, while maintaining real-time performance and ensuring that they do not interfere with each other. We then designed a randomized controlled study with healthy volunteers to assess the potential of multimodal EEG-fNIRS NF. We hypothesize that presenting participants with visual NF based on a combined score from both EEG and fNIRS signals will result in higher sensorimotor brain activity reflected in both EEG and fNIRS signals. As exploratory outcomes, we will investigate the participants’ feeling of NF control, the relationship between the motor imagery vividness (i.e., ability to build image and kinesthetic sensation of a movement) and the NF score. We will start by presenting the designed and already operational experimental platform and will then present the study protocol proposed to evaluate the effects of EEG-fNIRS based NF.

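### The primary outcome, brain activity, is not reduced to one measure or a success rule, while its candidate measures all fall under an unadjusted p < 0.05

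*Protocol article*

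**What the plan says.** Protocol article, section 2.2.5 (Statistical analysis):

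- One significance level covers everything, and the primary outcome is a domain, not a variable: "A significance level of p < 0.05 will be used for all analyses. The primary outcome will be the difference in the brain activity". The comparison is across the feedback conditions.
- Four data types are given as its content: "brain activity data (i.e., EEG-ERD, EEG-ERS, fNIRS-HbR, fNIRS-HbO_2_), the Shapiro-Wilk test will be conducted". Conditions are then compared by repeated-measures ANOVA or, if the data are not normal, by Friedman tests.

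Section 2.2.4 (Data and outcome measures), paragraph on brain activity, expands the four types. For fNIRS: "We will examine changes in the average, peak and area under the curve of ΔHbO_2_ and ΔHbR concentration", on the right and the left side. For EEG it lists the magnitude and ratio of alpha and beta power in both hemispheres, and then ERD and ERS for the alpha and beta rhythms.

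The hypothesis appears in two forms. In section 1 (Background), combined feedback "will result in higher sensorimotor brain activity reflected in both EEG and fNIRS signals". In the Discussion paragraph of the Abstract, it "will result in more specific task-related brain activity in the sensorimotor cortices". Neither is turned into a decision rule.

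**The concern.** A 5% level protects a study's main claim only if the claim rests on one defined test, on a rule that combines several tests, or on an adjustment across them. Here the primary outcome covers several measured quantities, each can be tested at 0.05, and nothing says which result, or how many, would confirm the hypothesis. Any significant member of the family could therefore be reported as the primary finding.

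This is more than detail left to an analysis plan. The article itself fixes the primary outcome and the significance level, and an adjustment introduced later would contradict a level that is said to apply to all analyses.

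A related gap concerns what a significant result would mean. ANOVA and Friedman tests across three conditions are omnibus tests. A small p-value could arise from EEG-only against fNIRS-only feedback, with no benefit of combining the two. The aim in section 1 is a comparison of combined feedback with each single modality.

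**Working it through.** The article states no power, sample-size calculation or family-wise error rate, so there is no figure of its own to reproduce.

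**Step 1. Count the candidates (section 2.2.4).**

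- fNIRS: 3 summaries (average, peak, area under the curve) × 2 chromophores × 2 hemispheres = 12.
- EEG ERD/ERS: 2 × 2 bands = 4. If also split by hemisphere, 8; the sentence on ERD/ERS does not mention hemisphere.
- EEG power: 2 (magnitude, ratio) × 2 bands × 2 hemispheres = 8.

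Totals: 12 + 4 = 16; 12 + 8 = 20; 12 + 4 + 8 = 24; 12 + 8 + 8 = 28. Section 2.2.5 on its own names 4 types.

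**Step 2. Independent tests, no true difference, any one significant result counts.** The chance of at least one p < 0.05 among k tests is 1 − 0.95^k.

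| k | Chance of at least one |
|---|---|
| 1 | 5.0% |
| 4 | 18.5% |
| 16 | 56.0% |
| 20 | 64.2% |
| 28 | 76.2% |

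**Step 3. Correlated measures.** The documents give no correlations, so these values are assumptions. The simulation used 30 participants (section 2.2.1), 3 conditions, a repeated-measures ANOVA F test at 0.05 and 6,000 replicates under no effect.

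| Common correlation | 20 measures | 4 measures |
|---|---|---|
| 0.3 | 55% | 18% |
| 0.5 | 43% | 16% |
| 0.7 | 31% | 13% |
| 0.9 | 16% | 9% |

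At 0.95, 20 measures still give 12%. With correlation only within each modality and none between, 20 measures give 58%, 50%, 40% and 25% at 0.3, 0.5, 0.7 and 0.9. A nested pattern gives 45%: 0.9 among the three summaries of one fNIRS signal, 0.5 elsewhere within a modality, 0.1 between modalities.

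**Step 4. Where the figure for 20 measures passes 50%.** Interpolating between 54.5% at 0.3 and 42.8% at 0.5: 0.3 + 0.2 × (54.5 − 50)/(54.5 − 42.8) = 0.38. Above a common correlation of roughly 0.35 to 0.4, the chance is below one half.

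**Step 5. A different reading: at least one significant measure in each modality.** With 8 EEG and 12 fNIRS measures, independent: (1 − 0.95^8) × (1 − 0.95^12) = 0.337 × 0.460 = 15.5%. Across the correlated cases this ran from about 2% to 16%.

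**Step 6. After repair.** One named primary test gives 5.0%. Bonferroni over 20 measures uses 0.05/20 = 0.0025 per test, so 1 − 0.9975^20 = 4.88% if independent, and at most 5% under any correlation.

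**The case against.** The strongest reply is that the article never says that any one significant measure is enough. The Background expects an effect in both signals, and step 5 shows that a rule requiring at least one significant result in each modality gives a much lower error, in some correlated cases below 5%. That stands as a limit on the size of the problem. It does not remove the problem, because the expectation is not written as a decision rule.

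The count is also open to challenge. Section 2.2.4 lists measures to be examined or calculated, and that each is formally tested is inferred from the level set for all analyses. Over a fixed 15 s task, area under the curve equals average × 15 s if both are signed and use the same window (an assumption). The 12 fNIRS measures then shrink to 8, and the total without power measures to 12 (46.0% if independent) or 16. Taking only the right side, which holds the stated target area, leaves 4 fNIRS + 4 ERD/ERS = 8 (33.7%). Adding the power measures moves the count the other way, to 24 or 28. So a reader might infer that at least 20 primary tests are planned, but the text does not fix that number.

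The two wordings of the hypothesis are a lesser matter: one is an abstract, and no error rate depends on them. It is also fair that this is a single-session study in healthy volunteers, that section 2.2.5 already separates exploratory outcomes from the primary one, and that an unseen analysis plan might contain a multiplicity method. The undefined primary outcome and the flat 0.05 are nevertheless fixed in this article.

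**Conclusion.** The point holds in conditional form. The primary outcome is not reduced to one measure or success rule: four data types in section 2.2.5 become roughly 16 to 28 overlapping candidates in section 2.2.4, at 0.05 without adjustment. As written, the plan does not secure the 5% level for its main claim.

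The size depends on two things that the documents do not give: the success rule and the correlations. Under every any-one-counts case with more than one measure examined here the error exceeded 5%, from about 9% (four measures at correlation 0.9) to 64% (20 independent measures) and 76% (28 independent measures).

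A reader might go further and infer that a positive primary result is likely even if the conditions do not differ. The documents do not support that. It needs an any-one-counts rule that they never state and, for 20 measures, a common correlation below about 0.35 to 0.4. Several candidates, such as average, peak and area under the curve of one signal, are probably strongly correlated.

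**What to change.** Amend section 2.2.5 and date the change before the condition comparison is seen. Section 2.2 has acquisition running from 1 December 2024 to 30 June 2025, so a primary variable chosen after that comparison would itself be post hoc and should be labelled so.

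1. **Name the primary variables.** One choice that the article already supports is the pair of feedback targets in section 2.1.2: alpha ERD at the C4 Laplacian, and mean task-minus-rest HbO2 in D1-S1/D2-S2, each averaged over the two runs.
2. **Name the directional contrasts:** EEG-fNIRS against EEG-only, and EEG-fNIRS against fNIRS-only. An omnibus test alone cannot show a multimodal benefit.
3. **State the success rule.** Following the Background, claim success only if both signals favour EEG-fNIRS on both contrasts. That is 2 × 2 = 4 tests, each at 0.05. No alpha split is needed: if any one of the four null hypotheses is true, success requires that test to reject, which happens at most 5% of the time. A single primary measure, or Holm across a stated primary family, would also repair the defect.
4. **Reclassify the rest.** Beta, ERS, HbR, peak, area under the curve and left-hemisphere measures become secondary with adjustment, or exploratory. Limit the blanket statement on 0.05 accordingly.

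The cost is wording only, with no new data. Fewer results can be called primary, and requiring both signals is stricter and lowers power.
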